### Trial Aims and Objectives

The present project aims to evaluate the efficacy of FR in improving psychosocial functioning, cognitive deficits and the quality of life in a sample of euthymic patients diagnosed with BD. This intervention will be compared with a control condition: a group of participants will follow a treatment as usual (TAU) program that includes only pharmacological treatment according to good clinical practice.

The primary objective measure is the score on the Functioning Assessment Short Test (FAST) from the baseline to the endpoint. The hypothesis is that an integrated treatment (FR + TAU) may be more effective than the standard treatment (TAU) in improving psychosocial functioning in BD. We hypothesize that patients involved in an FR group will show improvements in overall psychosocial functioning compared to patients included in the control group (TAU).

One secondary objective is to evaluate whether integrated treatment (FR + TAU) can allow a more effective response in improving neurocognitive and socio-cognitive performance and subthreshold affective symptoms compared to standard treatment (TAU). A further secondary objective is the identification of possible sociodemographic, clinical, cognitive and functional predictors of clinical, cognitive and functional responses in the two groups of patients.

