#### 2.3.1. Inclusion Criteria

Eligible participants will be fully informed about the study procedure and included only if providing written informed consent. They will be required to meet the following inclusion criteria: (a) age between 18 and 55 years; (b) education level of ≥8 years; (c) diagnosis of BD type I or II as referred from treating psychiatrist and confirmed at recruitment using the Structured Clinical Interview for Disorder for DSM-5, Clinical Version (SCID-5-CV) [52]; (d) clinical re0mission according to DSM-5 criteria (no mood episodes for ≥2 months) [53]; (e) euthymic phase at baseline assessment (defined as scoring both ≤6 points on the Young Mania Rating Scale (Y-MRS) [54] and ≤8 points on the Hamilton Depression Rating Scale (HAM-D)) [55]; (f) moderate to severe degree of functional impairment (defined as a score of ≥18 points on the Functioning Assessment Short Test (FAST)) [56]; (g) adequate mastery of Italian language, spoken and written.

According to these criteria, participants will not be pre-screened for neurocognitive impairment since the main focus of FR is functioning rather than cognition, and this program is primarily (though not exclusively) aimed at promoting psychosocial functioning among patients with significant impairment in occupational and interpersonal domains [15].

Concomitant medications will be kept stable as much as possible throughout the trial in order to reduce confounding effects. For patients receiving lithium therapy, the serum dose will be monitored over time and maintained within the therapeutic range. No major restrictions will be applied in terms of medication doses or compounds in order to not affect trial feasibility and the generalizability of the results; however, subsequent analyses are going to include the investigation of the potential influence of these parameters on treatment effect.

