Patients will be considered dropouts in the following cases: (a) withdrawal of consent; (b) emergence of a full-blown mood episode and/or major change in drug therapy needed in order to prevent this eventuality within the study period; (c) discontinuation of drug therapy for ≥5 consecutive days; (d) missing ≥5 consecutive FR sessions.

Additional information will be collected regarding demographic and clinical characteristics of the included participants: age, sex, employment status, familiarity for psychiatric disorders, BD type I/II, cycling, seasonality, age at onset, duration of illness, number of previous episodes, history of psychosis, history of suicide attempts, presence of baseline residual symptoms and baseline cognitive performance (BAC-A), current therapy (baseline medications, changes in medication within the study period, lithium (yes/no), antipsychotics (yes/no)) and global daily drug burden, estimated using the WHO defined daily dose (DDD) method [64].

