## 3. Measurement

### Statistical Analyses

All the analyses will be carried out using SPSS version 14.0 for Windows (SPSS Inc., Chicago, IL, USA, 2005).

Improvements in psychosocial functioning and cognitive performance will be assessed using effect size estimates obtained from within- and between-group differences at repeated measures analyses of variance (rm-ANOVAs). In case of attrition rate > 20%, a mixed model will be employed, under the missing at random (MAR) assumption. Regarding clinical symptoms, treatment effects will be compared among patients with and without residual symptoms (≥1 on Y-MRS, ≥3 on HAM-D) using t-tests.

Given the small sample size, the investigation of potential predictors of response through regression analyses should be considered largely explanatory. However, some regression analyses will be performed as deemed important in light of the feasibility nature of this trial; variables of interest will include participants’ age, duration of illness, baseline functioning, baseline cognitive performance and change in cognitive performance as well as potentially emerging predictors of dropout. In fact, participants leaving the study early will be compared with those completing all study procedures in terms of demographic and clinical variables using inferential statistics to assess potential moderators.

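### The stated analysis of Y-MRS and HAM-D is organised by residual-symptom status and gives no whole-sample FR-versus-TAU comparison, so it does not match the secondary symptom objective

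*Protocol article*

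**What the plan says.** Trial Aims and Objectives sets, as a secondary objective, the question whether the integrated treatment does better at "improving neurocognitive and socio-cognitive performance and subthreshold affective symptoms compared to standard treatment (TAU"). Section 2.7 lists Y-MRS and HAM-D among the secondary endpoints, and Section 2.6 places assessments at T0, T1 and T2.

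Statistical Analyses opens with the model for the other outcomes: "Improvements in psychosocial functioning and cognitive performance will be assessed using effect size estimates obtained from within- and between-group differences" from repeated-measures ANOVA, with a mixed model if attrition exceeds 20%. Symptoms are not named there. They get one sentence of their own: "treatment effects will be compared among patients with and without residual symptoms (≥1 on Y-MRS, ≥3 on HAM-D) using t-tests". That sentence does not say which variable is tested, at which visit, or whether arm enters. Section 2.7 lists the "presence of baseline residual symptoms and baseline cognitive performance (BAC-A") among the characteristics to be collected, which points to grouping by the baseline score.

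The same section later compares early leavers with completers "in terms of demographic and clinical variables using inferential statistics to assess potential moderators".

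**The concern.** The objective is a randomised contrast between FR + TAU and TAU. The stated analysis contrasts, or is at least arranged by, two groups formed on symptom score. Followed as written, the trial could finish without an overall between-arm estimate for two of its secondary endpoints.

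There is also a risk of a misleading positive result. Patients selected for a higher baseline score tend to score lower next time whatever treatment they receive. A t-test on change by baseline residual status can pick this up and be reported as a benefit in patients with residual symptoms.

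A smaller point of the same kind concerns the leaver/completer comparison. It identifies correlates of dropout. Moderation of the FR effect is a different question and needs an arm × covariate term.

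**Working it through.** **Plan's own figures.** No power or error figure is given for the symptom analysis. The only sample-size figure is for FAST: 44 patients, 95% power, f = 0.25. It reproduces with two groups, three visits and an assumed correlation of 0.5 between visits: λ = f²·N·m/(1−ρ) = 0.0625 × 44 × 3/0.5 = 16.5 on 2 and 84 df gives power 0.956. Allowing for 20% attrition, 44/0.8 = 55, against the stated 54. Nothing below depends on this; it supplies the sample sizes used.

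**What each reading of the symptom sentence delivers.**

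| Reading | Overall FR-versus-TAU estimate? | Tests whether the FR effect differs by residual status? |
|---|---|---|
| Symptom change, residual versus non-residual patients | No | No; arm does not enter |
| FR versus TAU within each stratum | No; two separate estimates | No; significance in one stratum and not in the other is not a test of difference |
| Arm × residual-status interaction | No, not by itself | Yes, but this is not the two-sample t-test named |

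No row supplies the contrast in the objective.

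**Size of the regression-to-the-mean problem under the first reading.** With equal variances and no true change, the expected change given the baseline score is −(1−ρ) × (baseline − mean). The two groups therefore differ in mean change by about −(1−ρ) × (gap in their baseline means), with no treatment effect at all. Rounding and the floor at zero make this approximate, so it was simulated.

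Inputs from the article:
- entry ceilings: "scoring both ≤6 points on the Young Mania Rating Scale (Y-MRS") and "≤8 points on the Hamilton Depression Rating Scale (HAM-D");
- residual cut-offs: ≥1 on Y-MRS and ≥3 on HAM-D, each scale split on its own cut-off;
- 1:1 allocation; N = 54 (target) and N = 44 (evaluable).

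Assumed, because the article does not give them:
- latent mean and SD of 3 and 3 for HAM-D, 1 and 2 for Y-MRS;
- latent test-retest correlation from 0.3 to 0.9;
- two-sided tests at 0.05, no treatment effect, no time effect.

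There were 2,000 trials per setting. Trials with fewer than three patients in any arm-by-stratum cell were dropped, leaving at least 1,993.

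HAM-D, N = 54, about 55% of patients with residual symptoms:

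| Correlation | Spurious difference in mean change (points) | Rejects: residual vs non-residual, both arms | Rejects: same, FR arm only | Rejects: FR vs TAU, all patients |
|---|---|---|---|---|
| 0.3 | −2.86 | 97.3% | 74.4% | 5.1% |
| 0.5 | −2.10 | 89.2% | 57.0% | 5.0% |
| 0.7 | −1.34 | 68.2% | 36.2% | 5.0% |
| 0.9 | −0.48 | 27.4% | 14.6% | 4.3% |

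With N = 44, the both-arms rejection rates at the same four correlations are 94%, 81%, 59% and 23% for HAM-D, and 90%, 76%, 54% and 24% for Y-MRS.

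**Other readings, same simulations, all settings:**
- FR versus TAU within each stratum: 2.7% to 6.0%.
- Arm × residual-status interaction on symptom change: 3.0% to 5.8%.
- Residual versus non-residual patients on an outcome simulated as independent of baseline symptoms (standing in for FAST change): 4.1% to 5.7%.

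The inflation therefore belongs to one combination only: change in the same scale, compared between groups formed on its baseline score.

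**The case against.** A reader might infer that the symptom objective is never tested between the arms. The text does not establish that. A treatment effect is by definition a between-arm contrast, so comparing treatment effects among patients with and without residual symptoms can mean FR versus TAU inside each stratum, or a moderator analysis. A reader might also infer that false positives are bound to follow. They follow only under the reading just isolated; under the others the error rate is nominal or slightly below. The inflated rates also rest on assumed means, SDs and correlations.

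The document is a condensed article, so an overall arm comparison may stand in a fuller plan. Y-MRS and HAM-D are two of several secondary endpoints in a trial that calls itself a pilot.

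On moderators, the article plans separate regressions for predictors of response and treats them as tentative given the sample size. The leaver/completer sentence follows directly on predictors of dropout, so the reference to moderators may be no more than loose wording.

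Most of this stands, and it limits the claim. It does not remove it. The article does not merely leave the symptom analysis out: it names the test, the grouping and the cut-offs, and under every reading the overall arm contrast is missing. A sentence whose possible meanings run from about 5% error to above 90% needs rewriting in any case.

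**Conclusion.** The point holds in limited form. The stated symptom analysis does not match the symptom objective: it is organised by a non-randomised characteristic, it states no whole-sample FR-versus-TAU comparison of Y-MRS or HAM-D, and the named t-tests do not test effect modification. That conclusion needs no assumed figures.

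The false-positive risk is conditional. On the literal reading it is about 27% to 97% for HAM-D with 54 patients, under the assumptions listed; on the alternatives it is near 5%. The article does not fix which reading applies, so the inflation is a risk of the wording and not an established property of the plan.

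The moderator wording is a minor fault. The primary FAST analysis and the sample size are unaffected. Severity: should be fixed, for secondary endpoints only.

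**What to change.** Before analysis:

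1. State an FR-versus-TAU comparison of Y-MRS and of HAM-D at T1 and T2 in all randomised patients, adjusted for the baseline score (ANCOVA or a mixed model).
2. Replace the residual-status t-test with an arm × residual-status interaction, labelled exploratory, with status defined at baseline and the outcome and visit named.
3. Describe the leaver/completer comparison as an analysis of attrition, not as a test of moderators.

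The cost is wording only. Both scales are already scheduled at all three visits and residual status is already collected, so no new data or patients are needed.

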#### Power—Sample Size Calculation

The required sample size was estimated based on power calculations performed on the software G*Power [65] and assuming an effect size of 0.25 on the ANOVA group × time interaction for the primary outcome (psychosocial functioning measured with the FAST scale). This effect size is in line with that observed in previous studies adopting similar procedures and intervention paradigm [39]. With alpha at 0.05, the effect size could be detected with 95% power when enrolling a sample of 44 participants (22 per group). Assuming 20% attrition, it was decided to set the recruitment target at 54 participants (27 per group).

## 4. Discussion

The main aims of the present work are to assess the efficacy of FR for euthymic BD in improving psychosocial functioning and non-social and social cognitive performance.

The expected results are that FR could produce a positive effect on both the functioning and cognitive performance of participants, which could in turn have a consistent effect in improving the real-world, daily life functioning of participants, with positive implications also for their global quality of life [13].

In line with recent evidence, another expected result will be potential improvements of daily functioning related to changes in social cognition performance [66].

These results could replicate and further validate the available findings regarding the effectiveness of FR [39] and add to the growing amount of evidence indicating that CR-inspired interventions can produce substantial benefits in people living with BD [37], also considering the heterogeneity of the severity of cognitive impairments that characterize BD [32,33]. Obtaining a greater amount of evidence indicating that FR, as well as other CR-inspired interventions, represents an effective treatment for BD could lead to its inclusion into national and international treatment recommendations and foster a more consistent implementation of these interventions into clinical practice.

It is also possible that the findings of the present study could not support previous evidence indicating that FR is effective in improving functioning and cognition in BD. In this case, this negative finding would not detract from the efficacy of the intervention and its evidence-based nature but rather point out that some patient-, treatment- or setting-related characteristics could act as negative moderators of effectiveness, highlighting the need to further explore the role of these factors [57]. Several factors influenced the effectiveness and the acceptability of CR in trials including people living with schizophrenia [27,28,29,30,67], and in fact, studying the role of potential moderators of effectiveness also represents a secondary aim of the present study.

The present study shows a number of strengths. First and foremost, FR represents a psychosocial intervention that is characterized by relatively low resource requirements; it can be easily implemented in everyday rehabilitative practice in most clinical contexts. In fact, CR has been shown to produce significant improvements in people living with schizophrenia also in a real-world clinical context, using already available rehabilitation facilities [68,69]. Moreover, the assessment tools adopted in the present study represent a comprehensive and validated but simple and not excessively time-consuming array of instruments, including the BAC-A [63], which is currently recommended by the Cognition Task Force from the ISBD [8,38]. Both these factors could consistently contribute to support the evidence regarding the practical feasibility and implementation of the intervention but also positively contribute to the replicability of the observed findings.

However, some limitations have to be taken into account. Given the exploratory nature of the present study, the small sample size could represent the main limitation; in fact, while power analyses were conducted in order to define the recruitment of a sufficiently large sample to accurately evaluate the primary aim of the study, there is the possibility that secondary analyses—particularly those regarding potential moderators of response—could be underpowered. This fact will be taken into account both during data analysis and during the discussion of observed findings. Another limitation that has to be mentioned is that the FR-integrated intervention will be compared to TAU, which will not allow to infer potential comparisons between FR and other evidence-based psychosocial interventions validated in the treatment of BD. Cognitive screening, which is recommended in some of the available methodological recommendations [8,38], does not represent an inclusion criterion for the study; considering the cognitive heterogeneity of BD, this could lead to the inclusion of cognitively intact subjects in the trial, which could in turn reduce the chance of detecting treatment efficacy. However, it has also been hypothesized that people living with BD could benefit from the therapy regardless of their neurocognitive profile. Moreover, the use of FAST as a screening tool could help in detecting patients for whom neurocognitive impairment does actually interfere in everyday life [13]. Finally, diagnosis of neurological conditions represents an exclusion criterion for the present study, as they might affect the ability to perform neuropsychological tests beyond the impairments that can be commonly observed in people living with BD. However, given the possible high comorbidity between BD and some neurological conditions, such as multiple sclerosis [70,71,72], the issue of potential comorbidity should be explored more in detail, and future dedicated trials, including genetic testing, could be devised to further investigate these aspects.

Future research perspectives also include further exploring the cognitive heterogeneity of BD, leading to the development of target interventions that could be easily and practically adapted to the cognitive profile of each individual. This would represent an important improvement also considering the need to further develop personalized treatments and intervention strategies, a goal which is becoming more and more important in modern and personalized psychiatry and precision medicine [73]. From this perspective, better understanding the impact of moderators of effectiveness could play an important role. Moreover, a longitudinal observation of participants could allow to assess the durability of effects of the treatment and also provide further insight on the impact of treatment on the clinical and cognitive progression of the disorder.

Another interesting future development could be the investigation of the effectiveness of FR specifically in participants in the early or very early stages of the disease; interventions in this population could have a significant impact on the trajectory of the disorder, and establishing whether cognitive-oriented treatments could have a protective effect in longitudinal evaluations represents an important future step [74].

Better investigating neurobiological factors on the structural, functional and molecular levels represents another important area of future development [13,75,76,77,78]. In fact, furthering the knowledge and understanding of the neurobiological and neuropathological mechanisms involved in BD in the context of cognitive treatment could lead to the identification of both general and specific markers of response. This could allow a better standardization of treatment response monitoring as well as of illness trajectories, also providing valuable insight into the issue of potential cognitive decline in long-term BD patients [79,80,81].

Finally, if the results of the present study confirm the effectiveness of FR in BD, FR could be integrated into structured rehabilitation programs and combined with other non-pharmacological interventions targeting cognitive performance and aiming for functional improvement, such as physical exercise [82,83,84,85,86] or neurostimulation [85]. Establishing whether combined interventions provide greater or faster improvements, as has been observed in trials including participants diagnosed with schizophrenia [86,87,88], could provide valuable information for clinicians and mental health services.

In conclusion, this study could represent a valuable contribution to the research field, providing interesting information on the effectiveness of FR in BD. Considering both psychosocial functioning and cognitive performance as relevant outcomes, the results of this study could provide further groundwork for the development of evidence-based targeted and tailored interventions for people living with BD.

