#### 2.4.2. Allocation and Blinding

Patients fulfilling all inclusion criteria will be randomized to the two parallel groups by a researcher not involved in the subsequent trial procedures, using a computer-based system (1:1 ratio). The allocation sequence will not be based on any stratification procedure, and all the details related to randomization will be kept locked following treatment allocation (Figure 1).

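### The Discussion settles in advance that a null FAST result would not count against functional remediation, which conflicts with the article's own 95% power claim

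*Protocol article*

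**What the plan says.** Under Trial Aims and Objectives, the primary hypothesis is that FR added to treatment as usual (TAU) "may be more effective than the standard treatment (TAU) in improving psychosocial functioning in BD", measured on FAST.

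The sample size section powers this hypothesis "assuming an effect size of 0.25 on the ANOVA" group × time interaction. It states 95% power at alpha 0.05 with 44 participants, and a recruitment target of 54 to allow for 20% attrition. The limitations paragraph of the Discussion repeats the claim in words: "power analyses were conducted in order to define the recruitment of a sufficiently large sample to accurately evaluate the primary aim of the study". The same sentence adds that secondary analyses, those on moderators in particular, could be underpowered.

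Earlier in the Discussion, positive results are said to be able to replicate and further validate the evidence for FR and to lead to its inclusion in treatment recommendations. The text then concedes that the findings might not support FR and says how that would be read: "this negative finding would not detract from the efficacy of the intervention and its evidence-based nature". It would instead indicate that some characteristics of patients, treatment or setting "could act as negative moderators of effectiveness".

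**The concern.** The two possible results are not treated alike. A positive result may count for FR, while a negative one is said in advance not to count against it. This sits badly with a trial described as large enough to evaluate its primary aim. If the power claim is right, a non-significant result is unlikely under the assumed effect and so carries information against it.

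The replacement explanation is also weak. A null average effect is what one sees when there is no effect. It is not by itself a sign that benefit in some participants has been offset or diluted in others. Moving from a null to moderators needs evidence of effect modification, and the article describes its own analyses of that kind as possibly underpowered.

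At stake is what the trial may conclude from a null: that a benefit of the planned size was not supported in this population and setting, or only that something unspecified got in the way.

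**Working it through.** **Inputs.** From the sample size section: f = 0.25 on the group × time interaction, alpha 0.05, 95% power, 44 participants (22 per group), 20% attrition, 54 recruited. From section 2.6: three assessments (T0, T1, T2). Two groups, allocated 1:1 (section 2.4.2). Not stated: the correlation ρ among repeated FAST scores and any non-sphericity correction. I assume ε = 1 and ρ = 0.5, and show ρ from 0 to 0.7.

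**Formula.** Repeated-measures within-between interaction, noncentral F, with k groups and m time points:

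- λ = f² × N × m / (1 − ρ)
- df1 = (k − 1)(m − 1) and df2 = (N − k)(m − 1)

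**Reproducing the plan's figure.** With N = 44, k = 2, m = 3 and ρ = 0.5:

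- λ = 0.0625 × 44 × 3 / 0.5 = 16.5
- df = 2 and 84; critical F = 3.105
- power = 0.956

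44 is the smallest even N that reaches 95% under these inputs, so the stated figure reproduces. With two time points the same inputs would need 54 analysed, so 44 fits the three-assessment design. For attrition, 44 / 0.8 = 55 against the stated 54, which is close enough not to matter here.

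**What a non-significant result would mean.** If f = 0.25 is true, the chance of a non-significant result is 1 − power. If there is no effect, it is 0.95. Their ratio shows how far a non-significant result favours the assumed effect over no effect; below 1, it counts against the assumed effect.

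| Assumed ρ | λ | Power at N = 44 | Non-significant if f = 0.25 | Ratio to 0.95 |
|---|---|---|---|---|
| 0 | 8.25 | 0.715 | 28% | 0.30 |
| 0.3 | 11.8 | 0.865 | 14% | 0.14 |
| 0.5 | 16.5 | 0.956 | 4% | 0.05 |
| 0.7 | 27.5 | 0.998 | 0.2% | 0.002 |

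At exactly the stated 95% power the miss rate is 5% and the ratio is 0.05 / 0.95 = 0.053. Every row is well below 1. The unstated correlation changes how strongly a null counts against the assumed effect, but not whether it does.

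**Setting the statements side by side.** The sample size section and the limitations paragraph say the primary aim can be evaluated well. The earlier Discussion sentence says a failure on that aim would not detract from efficacy. If the power statement holds, a null is evidence against an effect of the planned size, and the sentence on negative findings is wrong as worded. The same limitations paragraph says moderator analyses could be underpowered, and the statistical analysis section limits the weight of its predictor regressions because the sample is small. So the explanation offered for a null is the one this trial is less able to examine.

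**The case against.** The strongest case on the other side has four parts.

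1. **The test is untouched.** The sentence is Discussion prose and changes no endpoint, alpha, population or analysis. This stands. A reader might infer that the trial has been made unable to refute its primary hypothesis. The documents do not support that: FR + TAU against TAU on FAST can still come out null, and the Discussion itself says so. The asymmetry lies in the inference about efficacy.

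2. **The wording is partly hedged.** Moderators only could be at work, and positive results only could validate FR. This is true of those clauses. It is not true of the clause saying that a negative finding would not detract from efficacy, which is flat.

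3. **Setting and delivery factors differ mainly between trials.** The cited FR trial was multicentre, whereas this one runs in three units of one department. Such factors largely cannot be tested as an interaction within this trial, and the text only says they need further exploration. This also stands. A reader might infer that the authors intend their own underpowered moderator analyses to explain away the primary test; the text does not go that far. It does still name moderators as what a null would indicate, and a null alone does not indicate them. I give no single power figure for a moderator test, because it depends entirely on the size of interaction assumed.

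4. **One small pilot does not overturn earlier evidence.** The article calls the trial a pilot and exploratory, and says limited power for secondary analyses will be considered when findings are discussed. That view is defensible and may be kept. Saying that a negative result does not detract at all is a stronger claim, and it does not fit a trial said to have 95% power on its primary aim.

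**Conclusion.** The point holds as a fault of stated interpretation. The article announces an asymmetric reading of its primary result that contradicts its own power statement.

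Taking the stated 95% power at face value, a true f = 0.25 would be missed about 5% of the time, so a null would be strong evidence against an effect of that size in this population and setting. That strength is conditional. It reproduces with three time points, sphericity, 44 analysed and ρ = 0.5, and ρ is not given. With ρ of 0.3 or 0 the miss rate is about 14% or 28%, and a null is weaker evidence but still evidence against the assumed effect.

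A null would not show that FR has no effect of any size, nor that the earlier trial was wrong. A single null with a wide interval could be simply inconclusive. That is a further reason to tie the conclusion to the confidence interval and not to a reading fixed beforehand.

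**What to change.** Replace the sentence on negative findings with a symmetric statement, before results are known:

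- Report the between-group FAST effect with its 95% CI on the effect-size scale used for planning. The article gives no target in FAST points and no standard deviation, so a rule in FAST points cannot be applied from what is stated. Define f as in the power calculation and state the correlation used. Because f has no sign, give the direction from the arm means.
- If the interval excludes the assumed effect (f = 0.25 lies above its upper limit), conclude that a benefit of that size was not supported in this population and setting.
- If the interval includes both zero and the assumed effect, call the result inconclusive.
- Describe any moderator explanation of a null as hypothesis-generating.

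The text may still say that one small trial does not by itself overturn earlier evidence.

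The cost is a few sentences and one effect-size interval. Design, sample size and planned tests stay as they are. The downside for the authors is a less favourable stated reading of a null result.
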